## 5 TREATMENT OF SUBJECTS

### 5.1 not applicable

### 5.2 Investigational product/treatment

#### ***Reward modification tool***

The tool to modify reward experience, the intervention, is a technique called *Mindfulness-based Cognitive Therapy* (MBCT). During MBCT, people are trained towards increased moment-to-moment awareness of experience, resulting in increased openness or receptiveness. This training is based on meditation techniques to train deployment of attention in a way that subjects learn to focus attention on the present (to be mindful). Thus, during MBCT people train (by doing attention exercises) the ability to focus or detach attention. This will help people to remain open to what is there, to experience it fully without aversion or attachment. In that sense, the training is not like psychotherapy and does not involve talking about life experiences. Although many studies show that MBCT is effective in reducing depressive symptoms and relapse probability, the mechanism remains unknown. MBCT is also used for treatment of chronic pain or burn-out and in healthy subjects to increase wellbeing. I hypothesise that MBCT is a tool that increases the ability to make use of natural, moment-to-moment rewards in the environment.

### 5.3 Use of co-intervention (if applicable)

Not applicable

### 5.4 Escape medication (if applicable)

## 6 INVESTIGATIONAL MEDICINAL PRODUCT

Not applicable

## 7. METHODS

### 7.1 Study parameters/endpoints

#### 7.1.1 Main study parameter/endpoint

-The increase in reward experience in daily life, where reward experience is conceptualized as the effect of small positive daily life events on positive mood.

Since ESM is measures are performed 10 times a day for 6 days, there will be a maximum of 60 measurements within each subject concerning the effects of positive events on positive mood in the flow of daily life.

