**Objective:**

- 1) Can the ability to experience reward in daily life be experimentally modified?
- 2) How does experimental modification of reward impact on depressive symptomatology and can individual variation be traced to genetic variation.

**Study design:** An intervention study is used in which subjects are randomized to treatment as usual (TAU) or TAU + mindfulness-based cognitive therapy. Experience Sampling Method (ESM) is a structured diary, momentary assessment technique to study subjects in their daily life. Before and after the intervention subjects undergo a six-day period of ESM assessment. Subjects will be globally informed, but remain blind as to how ESM measures relate to testing the hypothesis.

**Study population:** A sample of 120 depression-remitted adult subjects with residual symptomatology (Ham-17>7) recruited from the community mental health centre in Maastricht (CMHC).

**Intervention (if applicable):** The experimental group receives 8 weeks of mindfulness training by an experienced trainer in addition to their normal treatment, if any. Sessions are weekly (2,5 hours a session) and subjects receive daily homework exercises. The control group continues their normal treatment, if any.

**Main study parameters/endpoints:** The increase in reward experience in daily life, whereby reward experience is conceptualised as the effect of small daily life positive events on positive mood state. Since ESM measurements are performed 10 times a day for 6 days, there will be a maximum of 60 measurements within each subject concerning effects of positive events on positive mood state in the flow of daily life.

**Nature and extent of the burden and risks associated with participation, benefit and group relatedness:** There are no health risks associated with participation. There is a personal benefit for subjects in that they are randomized to receive an extra training that is expected to improve their resilience against depression. Time investment for subjects is 2,5 hours for questionnaires (distributed over three meetings, including the screening). In addition, they participate twice in the ESM protocol (6-day period of filling in dairies concerning daily life events and mood). Before the start each ESM protocol they have to come for a short meeting (15 -30 min) to receive specific instructions related to this

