## 4. STUDY POPULATION

### 4.1 Population (base)

A sample of 120 depression-remitted subjects with residual symptomatology will be included, recruited from the CMHC in Maastricht, The Netherlands.

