#### 7.1.3 Other study parameters (if applicable)

Possible moderators of main study parameter:

- number and recency of previous depressive episodes
- age of onset first depressive episode
- life events and childhood trauma
- personality

Possible confounders/mediators:

- amount of rumination
- baseline and change in negative affect

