### 7.2 Randomisation, blinding and treatment allocation

Subjects are randomized to MBCT + treatment as usual (experimental group) or treatment as usual (control group). Randomization takes place after the baseline measurements and first week of ESM. This is because ESM measurements are not

considered valid in case <30% of the responses are valid. Subjects that have not enough valid ESM response are excluded from the study before randomization. Subjects are obviously not blind to their treatment allocation, however, they do remain blind as to how ESM measures relate to testing the hypothesis.

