### **9.2 Univariate analysis**

Analyses are corrected for possible confounders, thus only multivariate analyses will be used.

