### **9.3 Multivariate analysis**

ESM data have a hierarchical structure. Thus, multiple observations (level 1) were clustered within subjects (level 2). Multilevel analysis takes the variability associated with each level of nesting into account . The XT MIXED command in STATA 9.1 (Statacorp, College Station, Tex) was used to perform multilevel linear regression analyses.

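### The main parameter is the increase in reward experience, and baseline reward experience, measured before randomisation, is not named for adjustment; naming it would gain precision at almost no cost

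*Protocol*

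**What the plan says.** The Protocol Summary, under main study parameters, defines the outcome as "The increase in reward experience in daily life, whereby reward experience is conceptualised as the effect of small daily life positive events" on mood. Section 7.1.1 again names "The increase in reward experience in daily life" as the main parameter, and in full reads: "The increase in reward experience in daily life, where reward experience is conceptualized as the effect of small positive daily life events on positive mood". Section 7.1.2 uses the same increase in the secondary parameters.

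On timing, section 7.2 states: "Randomization takes place after the baseline measurements and first week of ESM". People with too few valid ESM responses (under 30%, that is under 18 of 60) are removed before randomisation.

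On adjustment, section 9.2 gives a general rule: "Analyses are corrected for possible confounders, thus only multivariate analyses will be used". Section 7.1.3 lists the possible confounders or mediators: the amount of rumination, and "baseline and change in negative affect". Baseline reward experience is not in that list, nor among the possible moderators.

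On the model, section 9.3 says that a Stata mixed-model command "was used to perform multilevel linear regression analyses", with beeps nested in subjects. It gives no fixed or random terms and no primary contrast. On size, section 4.1 says: "A sample of 120 depression-remitted subjects with residual symptomatology will be included".

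**The concern.** Reward experience is a within-person regression slope estimated from at most 60 beeps per period, and possibly from as few as 18. Such a slope carries sampling error, which lowers the correlation between a person's two slopes. A change score subtracts the whole baseline slope, error included. When the correlation is below 1, only part of a baseline difference carries over to follow-up, so subtracting all of it adds noise and over-corrects any chance imbalance between the arms.

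Because randomisation follows the baseline week, the arms have the same expected baseline slope. A baseline-adjusted comparison uses that fact; a comparison of changes does not. At stake is precision on the primary question. The sample is 120, people who leave after randomisation are not replaced (section 7.5), and section 4.4 states no power for the primary effect.

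**Working it through.** **The plan's own figure.** The only power figure, in section 4.4, is 80% for a gene-by-training interaction of size 0.4. It cannot be reproduced, because the significance level, genotype split, within-person correlation, scale of the 0.4 and dropout rate are not given. It also does not concern the contrast examined here, so the check below is independent of it.

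**Inputs.** From the protocol: N = 120, two arms, the baseline slope measured before randomisation. Assumed, because not given: 60 per arm, equal slope variance s² in the two periods, pre-post slope correlation rho, two-sided 5% level, and an effect of 0.4 SD of the follow-up slope (used only to illustrate power).

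**Formulas, per subject.**
- Change score: variance = 2(1-rho)s².
- Baseline-adjusted: variance = (1-rho²)s².
- Ratio, adjusted to change: (1-rho²)/[2(1-rho)] = (1+rho)/2. The reduction is therefore (1-rho)/2.
- Power, normal approximation: Φ(0.4/(SD × √(2/60)) - 1.96), with √(2/60) = 0.1826.

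**Example at rho = 0.4.** Change: SD = √1.2 = 1.095, and 0.4/(1.095 × 0.1826) = 2.00, power 52%. Adjusted: SD = √0.84 = 0.917, and 0.4/(0.917 × 0.1826) = 2.39, power 67%.

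| rho (assumed) | Change variance /s² | Adjusted variance /s² | Reduction | Power, change | Power, adjusted |
|---|---|---|---|---|---|
| 0 | 2.00 | 1.00 | 50% | 34% | 59% |
| 0.2 | 1.60 | 0.96 | 40% | 41% | 61% |
| 0.4 | 1.20 | 0.84 | 30% | 52% | 67% |
| 0.6 | 0.80 | 0.64 | 20% | 69% | 78% |
| 0.8 | 0.40 | 0.36 | 10% | 93% | 95% |
| 0.9 | 0.20 | 0.19 | 5% | over 99% | over 99% |

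**Cost of the extra coefficient.** Estimating it inflates the adjusted variance by about 1 + 1/(120-5) = 1.009. At rho = 0.4 the ratio becomes 0.70 × 1.009 = 0.706, a net reduction of about 29%. The table does not include this factor. Adjustment still wins as long as 1.009 × (1+rho)/2 < 1, that is for rho below about 0.98.

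**Simulation check.** With 60 per arm and 20,000 runs, the reductions were 39.8%, 29.2%, 19.8% and 9.3% at rho 0.2, 0.4, 0.6 and 0.8, in line with 40%, 30%, 20% and 10% less about 1% of variance.

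**Does adjustment change the parameter?** If post = a + t·arm + b·pre, then post - pre = a + t·arm + (b-1)·pre. The arm effect t is the same. The simulation agreed to within 1e-15.

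**The case against.** The strongest reply is that the protocol never prescribes an unadjusted comparison. A reader might infer one from the word increase, but the text does not support that: section 9.2 calls for adjusted analyses only, section 9.3 gives no model terms, and, as the identity above shows, an increase adjusted for its baseline is still an analysis of the increase. Baseline reward experience is neither named nor ruled out. The covariates of a primary model are commonly left to the statistical analysis plan, which was not available here, so their absence is not a fault. This stands, and it limits the point to an improvement. It does not remove it: sections 7.1.3 and 9.2 do name adjustment variables, and followed as written they lead to a comparison of changes without this covariate.

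Other stronger readings are tempting and should also be resisted:
- A reader might take a 20% to 40% gain as established. It holds only for rho between 0.2 and 0.6, and the protocol gives no correlation, SD or reliability for the slope.
- A reader might think the change estimate biased. Under randomisation it is not; it is only less precise.
- A reader might conclude that the increase should become merely descriptive. It need not, and section 7.1.2 relies on it.
- A reader might extend the point to HAM-17 and SCL-90. Section 7.1.2 defines no arm comparison of either scale, only an association between increase in reward experience and decrease in symptoms.

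Finally, at low rho most of the gain comes from no longer subtracting a noisy baseline. Relative to follow-up alone the gain is rho², only 4% at rho = 0.2. That is true, but it does not weaken the comparison with a change score.

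**Conclusion.** The point holds as a free improvement, not as an error. If the arms are compared on the change alone, the estimate is valid but gives up a share (1-rho)/2 of its variance, less about 1%, that adjustment for the baseline slope would recover. With equal variances the direction does not depend on rho, except when rho is almost 1; the size does, and rho is unknown. The power figures further assume 60 per arm and an effect scaled to the follow-up slope; the 0.4 in section 4.4 belongs to a different contrast on an unstated scale. The formula describes two-step subject slopes; in the planned multilevel analysis the corresponding gain comes through the model constraint described below.

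**What to change.** Keep the increase as the named main parameter. Add one sentence to section 7.1.1 or 9.3 stating that the arm comparison is adjusted for baseline reward experience, and choose one of two routes:

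- In the multilevel model, constrain the arms to a common baseline level and a common baseline event slope, so that the arm enters only through the follow-up period. The random event slopes should be allowed to differ between periods and to correlate.
- In a two-step analysis, estimate each person's slope per period and enter the baseline slope as a covariate.

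The cost is that sentence and one estimated coefficient. No further patients or data are needed, since everyone randomised has already passed the baseline ESM validity check. If the statistical analysis plan already specifies this adjustment, a cross-reference is enough.

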#### 7.1.2 Secondary study parameters/endpoints (if applicable)

-The association between increase in reward experience and decrease in depressive symptomatology.

- The association between individual variation in reward experience (or increase in reward experience) and genetic variation in polymorphisms related to the brain reward system.

Genetic variation is measured in the collected saliva. Since insights concerning relevant polymorphisms and haplotypes change rapidly, an up-to-date relational (i.e. cross-relating genotype, phenotypic expressions, biochemical pathways) database relevant for the neurosciences is maintained within our department. Genetic analyses thus are always matched against the most recent information. According to current scientific knowledge we would decide to measure polymorphisms in the dopamine receptor 2 gene, the catechol-O-methyl transferase (COMT) gene, human kappa opioid receptor gene and the brain-derived-neurotrophic factor (BDNF) gene.

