## 2 OBJECTIVES

Primary Objective:

Can the ability to experience positive emotions from everyday life situations assessed with ESM (reward experience), be experimentally modified?

Secondary Objectives:

- ii) Will experimentally induced increases in reward experience in daily life reduce depressive symptoms in patients with residual symptomatology?
- iii) Are polymorphisms of genes coding for key proteins in the mesolimbic reward system associated with reward experience in daily life and acquisition of this ability?

Depressed subjects with (prevalent and harmful) residual symptomatology will be examined. The rationale for this is that examining modification of reward experience in these subjects may additionally shed light on its clinical relevance, i.e. the degree of associated reduction of residual symptoms.

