### 7.3 Study procedures

First, subjects are screened for the participation criteria and fill in a questionnaire concerning demographic variables.

At baseline subjects:

- undergo Psychiatric interviews: SCID-I and the Hamilton Depression Rating Scale (HAM-17).
- fill in some questionnaires concerning depressive symptoms (SCL-90), personality (NEO-PI) rumination (RRS), life events (Interview for Recent Life Events) and early adversity (Childhood Trauma Questionnaire)
- spit some saliva in special tubes as to measure polymorphisms/haplotypes in the DNA that have been associated in previous studies with the brain reward system. (Since insights concerning relevant polymorphisms and haplotypes change rapidly, an up-to-date relational (i.e. cross-relating genotype, phenotypic expressions, biochemical pathways) database relevant for the neurosciences is maintained within our department. Genetic analyses thus are always matched against the most recent information).
- participate in the 6-day ESM period as described under 'study design'. Subjects will be briefed and de-briefed before and after the ESM period, respectively.

Subjects randomized to the experimental group will participate in an 8-week-period of MBCT, including weekly sessions of 2,5 hours in which the training takes place and daily homework exercises. They also fill in to what degree they complied with the homework exercises every day (in minutes).

After the intervention, subjects from both groups (experimental and control) again undergo the psychiatric interviews and the questionnaires.

In addition, they participate in another 6-day ESM period and are again briefed and de-briefed with respect to this procedure. The ESM debriefing includes the collection of the diaries and discussion concerning unclarities or missing values.

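### A causal secondary objective on depressive symptoms is served only by an association between two concurrent changes, and no comparison of symptoms between the randomised arms is listed as an endpoint

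*Protocol*

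**What the plan says.** Secondary objective ii in Protocol section 2 is causal: "Will experimentally induced increases in reward experience in daily life reduce depressive symptoms in patients with residual symptomatology". The Summary's second objective is similar: "How does experimental modification of reward impact on depressive symptomatology". The same section 2 also uses softer wording when it explains the choice of population: "the degree of associated reduction of residual symptoms".

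The main endpoint (section 7.1.1) concerns reward experience, not symptoms: "The increase in reward experience in daily life, where reward experience is conceptualized as the effect of small positive daily life events on positive mood". The secondary endpoint that serves objective ii (section 7.1.2) is "The association between increase in reward experience and decrease in depressive symptomatology". It mentions neither the randomised arm nor an instrument for depressive symptoms.

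Section 7.3 lists HAM-17 and SCL-90 at baseline and continues: "After the intervention, subjects from both groups (experimental and control) again undergo the psychiatric interviews and the questionnaires". Section 7.1.3 lists rumination and negative affect (baseline and change) as possible confounders or mediators. Section 9.2 says that analyses are corrected for possible confounders. Section 9.3 describes multilevel regression for the ESM data.

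**The concern.** Randomisation protects a comparison of the arms. It does not protect a correlation, across subjects, between two changes that both occur after allocation. With one assessment before and one after the intervention, the order of the changes cannot be told. Fewer symptoms may raise the response to pleasant events, or something else may move both.

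At stake is the claim that raising reward experience lowers depression. The endpoint could support that claim when no such effect exists. Meanwhile the one symptom result that randomisation does protect, MBCT plus usual care against usual care, has no place among the endpoints.

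**Working it through.** **Objective against endpoint**

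| Item | Section | Content |
|---|---|---|
| Question | 2 (ii); Summary | Does an induced increase in reward experience reduce symptoms? |
| Endpoint | 7.1.2 | Association of two changes within subjects |
| Symptom data | 7.3 | HAM-17 and SCL-90, before and after, both arms |
| Arm comparison of symptoms | 7.1.1 to 7.1.3 | None listed |

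The protocol's only power figure (section 4.4) is for a gene-by-training interaction. It has no bearing on this endpoint, so there is no figure of the plan to reproduce here.

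**Illustration 1: an association with no causal path**

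Inputs: N = 120 (section 4.1); two-sided alpha 0.05 and the non-causal correlation r are assumed. By Fisher's z, P(significant) = Φ(atanh(r)·√(N − 3) − 1.96), with √117 = 10.817.

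- r = 0.2: 0.2027 × 10.817 − 1.96 = 0.233, giving 59%.
- r = 0.3: 0.3095 × 10.817 − 1.96 = 1.388, giving 92%.

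Here r must be read as what remains after confounder correction. Suppose a shared cause gives r = 0.3 and the adjusting variable (say, change in negative affect) correlates c with that cause. The partial correlation is (0.3 − 0.3c²)/(1 − 0.3c²), and √(N − 4) = √116 = 10.770 replaces √117.

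- c = 0.7: 0.153/0.853 = 0.179; 0.181 × 10.770 − 1.96 = −0.006, giving about 50%.
- c = 0.8: 0.108/0.808 = 0.134; 0.1345 × 10.770 − 1.96 = −0.512, giving about 30%.

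Correction lowers the figure but does not bring it to 5%. The values of c are assumptions too.

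**Illustration 2: does putting arm in the model cure it?**

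In a simulation (4,000 replicates, 60 per arm, reward experience given no effect on symptoms, shared-cause correlation 0.25), the association was significant in 79% of trials both without and with adjustment for arm. The arm comparison of symptoms was significant in 5%, as it should be. Arm adjustment is still right, but it does not remove a cause shared within the arms.

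**Illustration 3: an effect on symptoms that the association does not show**

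Let MBCT improve both outcomes by 0.5 SD through separate paths with no shared cause. The arm effect adds 0.5² × 0.25 = 0.0625 to the covariance and to each variance, so the correlation is 0.0625/1.0625 = 0.059. The unadjusted association is then significant in about 9% of trials, while the arm comparison detects the symptom benefit in 76% to 78%.

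**Is the arm comparison feasible?**

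Assume 1:1 allocation (60 per arm) and two-sided alpha 0.05. Power = Φ(d/(√(1 − ρ²)·√(2/n)) − 1.96), where ρ is the baseline to post-intervention correlation of HAM-17 and √(2/60) = 0.1826.

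- d = 0.5, no adjustment: 2.739 − 1.96 = 0.779, giving 78%.
- d = 0.5, ρ = 0.5 (assumed): 2.739/0.866 − 1.96 = 1.202, giving 88%.
- Smallest difference with 80% power: 2.802 × 0.1826 = 0.51 SD unadjusted; × 0.866 = 0.44 SD adjusted.
- With 20% dropout (assumed; section 7.5 gives no rate), 48 per arm: 0.57 and 0.50 SD.

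A moderate difference is within reach of the planned sample.

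**The case against.** The strongest reply is that this is a mechanism trial. Section 5.2 treats the effect of MBCT on symptoms as already shown and its mechanism as unknown, so an arm comparison of HAM-17 would not answer objective ii. The second half of that stands: the arm difference shows that the training works on symptoms, not that reward experience is the route. But a mechanism claim needs more than a correlation of changes, and the wording of section 2 is causal.

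A second reply is that sections 7.1.3 and 9.2 provide for confounder correction. This also stands in part. It means the 59% to 92% range is not a false-positive rate of this plan. Reward experience is moreover an effect of events on mood, not a mood level, so better mood need not change it. What remains is that correction for two listed factors cannot be relied on to remove every shared cause or to settle the order. Section 7.1.3 also leaves open whether they are confounders or mediators.

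Third, the SAP is not at hand and may add the comparison. The choice of endpoint, however, is made in section 7.1.2 of the protocol and does not match the protocol's own objective.

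Three stronger readings are tempting and are not supported:

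- A reader might infer that the trial would not report the arm effect on symptoms. The protocol says only which endpoints are listed, and section 11.5 commits to publishing positive and negative results.
- A reader might infer that selection on HAM-17 above 7 creates the correlation by regression to the mean. Selection shifts the average HAM-17 change. It yields a correlation across subjects only if baseline fluctuations in HAM-17 and reward experience are themselves correlated, which is the shared-cause argument again.
- A reader might add that HAM-17 raters are unmasked. The protocol does not say who rates, and masking is a separate operational matter.

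**Conclusion.** The mismatch holds: a causal objective rests on an association that randomisation does not protect, and the protected symptom comparison is not an endpoint although its data are collected. This follows from the text and needs no assumed number. It affects a secondary objective and leaves the primary endpoint untouched, so it should be corrected but does not undermine the trial.

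How often a misleading association would arise is unknown. The 59% to 92% range rests on assumed residual correlations of 0.2 to 0.3 in 120 subjects and falls as confounder correction takes effect. The power figures for the arm comparison rest on 1:1 allocation and assumed correlations and dropout.

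**What to change.** In section 7.1.2 and section 9:

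- Add as a secondary endpoint the arm difference in post-intervention HAM-17, adjusted for baseline HAM-17, in all randomised subjects. Name HAM-17 as the instrument and SCL-90 as supportive.
- Keep the association between the two changes as exploratory, with arm in the model.
- Report any mediation estimate (arm → reward experience → HAM-17) together with its assumption of no unmeasured confounding.
- State that the arm comparison shows the effect of MBCT on symptoms and not that reward experience carries it. Word the conclusion on objective ii as an association unless the mediation assumptions are accepted.

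The cost is wording and one more secondary analysis; no subjects, visits or measurements are added. The downside is that the causal wording for the association is lost.
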